
#### Sample Size and Power

Based on a sample size of 30, the two-sided 95% confidence interval will not be wider than 0.373 standard deviations for the adherence rate and will not be wider than 0.374 for the retention rate at each follow-up visit. In addition, it will have a power of 80% to detect a change of 0.47 standard deviations from baseline over two follow-up visits for each of the markers investigated in the secondary and tertiary aims, assuming a within-subject correlation of 0.20 at a significance level of 5%.

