**Methods:**

A single-arm unblinded clinical trial will be conducted to determine the feasibility of conducting a 24-week comprehensive lifestyle modification intervention that targets weight loss and increased physical activity modeled on the Diabetes Prevention Program in 30 men on ADT for prostate cancer. Secondary aims are to determine the effect of the intervention on cardiometabolic markers and quality of life. The tertiary aim is to determine the effect of the intervention on markers of inflammation and angiogenesis, important mechanisms for prostate cancer progression. Participants will be recruited from the University of Arizona Cancer Center and the surrounding community. The intervention will be delivered weekly in person and over the phone for 16 weeks. For Weeks 16-24, participants receive weekly phone calls from the study health coach to motivate them to continue their lifestyle modification. Questionnaire and biological data are collected at baseline, 12 weeks, and 24 weeks. Body composition using dual-energy x-ray absorptiometry scans will be performed at baseline and end of study.

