**Results:**

Based on a sample size of 30, the two-sided 95% confidence interval will not be wider than 0.373 standard deviations for the adherence rate and will not be wider than 0.374 for the retention rate. In addition, the study will have a power of 80% to detect a change of 0.47 standard deviations from baseline for each of the markers investigated in the secondary and tertiary aims assuming a within-subject correlation of 0.20 at a significance level of 5%. The recruitment period is from October 2018 to April 2019.

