### Outcome Measures

#### Feasibility Measures

Aim 1 of this study is to determine feasibility and hence the outcome measures for this aim will be recruitment, retention, and maintaining protocol adherence by the participants. The recruitment goal is set at 30 participants recruited over a 6-month period. The retention goal is set at 80%, and the adherence goal is set at 75% participation. If 80% (24/30) of participants complete the trial, the retention goal for this trial will be achieved. If participants attend 75% of the intervention delivery visits (in-person and phone combined), they will be considered adherent to the protocol.

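### The stated 80% power for a 0.47 SD change is not supported for the change-from-baseline intervals planned at 12 and 24 weeks, and the SD, correlation and contrast behind it are undefined

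*Protocol article*

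**What the plan says.** Sample Size and Power opens with "Based on a sample size of 30" and states that "it will have a power of 80% to detect a change of 0.47 standard deviations from baseline over two follow-up visits for each" of the secondary and tertiary markers, "assuming a within-subject correlation of 0.20" and a 5% significance level. The Results paragraph of the abstract repeats the claim without the reference to two follow-up visits: "the study will have a power of 80% to detect a change of 0.47 standard deviations from baseline".

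Neither place defines the standard deviation, the pair of measurements to which 0.20 applies, the test, its sidedness or any allowance for dropout.

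The Statistical Analysis section measures each outcome at baseline, 12 and 24 weeks. It plans two-sided 95% confidence intervals for the change from baseline at each follow-up, plus a linear mixed model to explore the trajectory. On retention, Feasibility Measures says: "If 80% (24/30) of participants complete the trial, the retention goal for this trial will be achieved".

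**The concern.** A single-arm trial tests a within-man change. If the marker's SD is the unit, the correlation between visits is what converts it into the SD of a change. A correlation as low as 0.20 makes the change more variable than the marker itself, so 30 men should not detect as little as 0.47 marker SD with 80% power. If the SD of the change is the unit, a single-visit test does not use the correlation at all, and 30 men still fall short.

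This is the only efficacy planning figure in the document, and it is claimed for every marker. A reader could take a non-significant marker as evidence against a 0.47 SD effect that had an 80% chance of being found. The article also says the results will inform the design of later trials.

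**Working it through.** **Inputs.** n = 30, change d = 0.47 SD, r = 0.20, level 5% (Sample Size and Power). Two-sided, by visit (Statistical Analysis). n = 24 completers (Feasibility Measures).

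**Method.** If the tested quantity has SD k in the chosen unit, the one-sample t test has n − 1 degrees of freedom and noncentrality (0.47/k)·√n. Power comes from the noncentral t distribution. At 80% power the detectable standardized change is 0.529 for n = 30 and 0.597 for n = 24. Multiplying by k gives the detectable change.

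**Can the plan's figure be reproduced?** Several calculations come close to 80% at 0.47, and the text spells out none of them:
- Joint 2-df test of the two changes, SD of change, correlation 0.20 between changes, n = 30: noncentrality 30 × 0.47² × 2/1.2 = 11.05, power 81.1%, detectable change 0.464.
- Average of the two changes, SD of change, correlation 0.20, but n = 24: power 81.2%, detectable change 0.463.
- One-sided single-visit test, SD of change, n = 30: power 80.7%, detectable change 0.465. The correlation is not used.
- k = √(1 − r) = 0.894, n = 30: power 79.4%, detectable change 0.529 × 0.894 = 0.473. This k is not the SD of a difference, which needs 2(1 − r).

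**SD of each contrast (k).**
- A. One visit minus baseline, marker SD: √(2(1 − r)) = √1.6 = 1.265.
- B. Mean of both follow-ups minus baseline, marker SD: √(1 + (1 + r)/2 − 2r) = √1.2 = 1.095.
- C. One visit minus baseline, SD of change: 1.
- D. Mean of the two changes, SD of change, correlation c between changes: √((1 + c)/2), which is 0.775 for c = 0.20 and 0.866 for c = 0.5.

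For A with n = 30, for example, the noncentrality is (0.47/1.265) × √30 = 2.035.

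| Contrast | Power at 0.47, n = 30 | Power at 0.47, n = 24 | Detectable at 80%, n = 30 | Detectable at 80%, n = 24 |
|---|---|---|---|---|
| A: one visit, marker SD | 50.3% | 41.5% | 0.67 | 0.76 |
| B: mean of two visits, marker SD | 62.2% | 52.1% | 0.58 | 0.65 |
| C: one visit, SD of change | 70.1% | 59.7% | 0.53 | 0.60 |
| D: mean of two changes, c = 0.5 | 81.9% | 72.1% | 0.46 | 0.52 |
| D: mean of two changes, c = 0.20 | 89.5% | 81.2% | 0.41 | 0.46 |
| Joint 2-df test, c = 0.20 | 81.1% | 69.9% | 0.46 | 0.53 |
| Joint 2-df test, c = 0.5 | 71% | 60% | 0.52 | 0.59 |

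**Why c = 0.5 matters.** Both changes subtract the same baseline. With equal variances and the same correlation r between any two visits, their covariance is r − r − r + 1 = 1 − r and each variance is 2(1 − r). Their correlation is therefore 0.5 whatever r is. A value of 0.20 between changes needs a different correlation structure.

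**What would make 0.47 hold at n = 30 in marker-SD units.** r would have to be about 0.61 for A or about 0.47 for B. At r = 0.20, 80% power for 0.47 SD would need 59 men for A or 45 for B.

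**The case against.** The best defence is that the claim may be true on the authors' own definitions. The text speaks of a change over two follow-up visits, so the SD could be that of the change and 0.20 the correlation between the two changes. The averaged change then has 89.5% power with 30 men and 81.2% with 24, and the joint test has 81.1% with 30. A power statement fails only when power is below the stated level, and on these readings it is not. This stands, and a reader who concludes that the true power is 50% to 62% goes further than the document allows: that range belongs to the marker-SD reading. The shortfall with 24 completers likewise depends on the reading if the two changes are averaged.

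The defence does not reach the planned analysis. The Statistical Analysis section describes intervals visit by visit, with neither an averaged change nor a joint test, and at one visit power is at most 70% on either definition of SD. A one-sided test would reach 80.7% in SD-of-change units, but the planned intervals are two-sided. Optional baseline adjustment in the mixed model does not rescue the single-visit claim either. A residual SD of √(1 − 0.20²) = 0.980 gives 71.9%, and in a single arm that treats the baseline mean as free of sampling error. On the same basis the mean of two visits would give 91.4%, with the same reservation.

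It is also tempting to say that 0.47 came from leaving the factor 2 out of the variance of a difference, since √(1 − r) gives 0.473. Other calculations land nearly as close and the authors' calculation is not shown, so this is conjecture.

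Finally, the trial's primary aim is feasibility, the efficacy results will be reported as intervals that show their own precision, and no decision rule uses 0.47. That limits the seriousness of the point but does not make the figure right.

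**Conclusion.** The point holds in limited form. For the two-sided change-from-baseline interval at a single visit, 80% power at 0.47 SD is not supported: it is 50% or 70% with 30 men, and 41% or 60% with 24, for marker SD and SD of change respectively. In marker-SD units the mean of both follow-ups gives 62% or 52%. The figure can be met with 30 men in SD-of-change units by averaging the changes, or by a joint test if they correlate 0.20, but the Statistical Analysis section describes neither.

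These results assume t-based inference at a two-sided 5% level for each marker, equal variances over time and, in marker-SD units, a correlation of 0.20 between any two visits. The document does not fix one true power, nor does it show where 0.47 came from. This is a secondary-aim planning figure that should be corrected. It does not affect the feasibility aim.

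**What to change.** In the abstract's Results paragraph and in Sample Size and Power, state three things: whether the SD is that of the marker or of its change, which measurements correlate 0.20, and which contrast and test the power refers to. Then restate the change detectable with 80% power for 30 men and for the 24 completers:

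- Marker SD, correlation 0.20 between visits: 0.67 SD (30 men) and 0.76 SD (24 men) at a single visit; 0.58 and 0.65 SD for the mean of both follow-ups.
- SD of change, single visit: 0.53 SD (30 men) and 0.60 SD (24 men).

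If the authors meant an averaged or joint test of the two changes, they should say so, justify the correlation between changes, and add that test to the Statistical Analysis section so that the power statement and the analysis refer to the same quantity.

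The cost is a change of wording and, for the visit-by-visit analysis, a less favourable stated figure. No extra patients or measurements are needed.

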## Results

Results from this arm open label clinical trial will allow us to determine the feasibility of conducting a DPP based intervention in men on ADT for PCa. Results are expected to be available by October 2019 and will inform the development of future trials in this population.

## Discussion

### Principal Considerations

The Comprehensive Lifestyle Improvement Project for Prostate Cancer (CLIPP) is designed to investigate the feasibility and early efficacy of a comprehensive multimodality intervention modeled after the DPP on cardiometabolic risk factors and QoL, as well as markers associated with inflammation and angiogenesis in men treated with androgen deprivation therapy for prostate cancer. This will be the first study in literature to investigate the utility of a DPP-based intervention on cardiometabolic risk factors and pathways associated with tumor progression in men with PCa on ADT. Although ADT improves disease-free survival and overall survival in men with PCa [1,2], its adverse effects lower the individual’s QoL and contribute to higher mortality. If an effective intervention is identified to mitigate the adverse effects associated with ADT, it could potentially improve the individual’s QoL as well as reduce their risk of treatment-related mortality. Results from the CLIPP study have the potential to provide data on the effect of the lifestyle modification intervention on QoL, cardiometabolic risk factors, as well as markers of inflammation and angiogenesis. Results for the primary aim are expected to be available by October 2019.

### Strengths and Limitations

The strengths of this study lie in its application of an evidence-based and effective multicomponent lifestyle modification intervention. This intervention has been successfully adapted for other disease types including breast cancer with favorable results. The standardized intervention with proven success in multiple disease settings, including cancer, sets this study apart from other comparable studies in current literature. The limitations of this study include its non-randomized treatment assignment and lack of a control group. Since this is a feasibility study, this is an accepted study design and a randomized study with an appropriate control arm would be the next step based on the study results.

### Conclusion

Findings from this study will address a critical gap in current literature by providing data regarding the feasibility of conducting a multimodality lifestyle modification intervention in men on ADT for prostate cancer and its impact on cardiometabolic risk factors, quality of life, as well as markers associated with inflammation and angiogenesis. These data are critical in developing future clinical trials in this group of patients. Additionally, the findings hold potential to open new avenues of research such as the impact of lifestyle modification on prostate cancer progression.

## Appendix

Multimedia Appendix 1 Study timeline.

Multimedia Appendix 2 Peer-review report.

Multimedia Appendix 3 Peer-review report.

## Abbreviations

ADT: androgen deprivation therapy
CLIPP: Comprehensive Lifestyle Improvement Program for Prostate Cancer
DPP: Diabetes Prevention Program
ELISA: enzyme linked immunosorbent assay
EPIC-26: Expanded Prostate Cancer Index Composite-Short Form
GnRH: gonadotropin-releasing hormone
IDEA-P: Individualized Diet and Exercise Adherence-Pilot
LEAN: Lifestyle Exercise And Nutrition study
PCa: prostate cancer
PROMIS: Patient Reported Outcomes Measurement Information System
QoL: quality of life
RR: relative risk
UACC: University of Arizona Cancer Center
